Expected adherence to multimodal care by patients will also be assessed at baseline using a specific questionnaire item (e.g. “I intend to perform the neck exercises that were prescribed for my condition”). Furthermore, compliance with guideline recommendations at the patient level will be measured using a checklist documenting the extent of their confidence in managing most of their health problems, the type of help received from their treating chiropractor, and the use of exercise and self-care prescriptions, as well as their levels of compliance with recommended exercises (Additional file 1). Furthermore, patient-related health outcomes will be collected at baseline and at 3 months through the use of questionnaires to measure symptoms, impairment, activity interference at home and at work, general quality of life, and satisfaction with care (PSQ-18). The minimal clinically important difference (MCID) in the 10-cm VAS pain score will be measured as the mean difference between current and baseline scores among patient participants who report feeling either “a little worse” or “a little better” in terms of their global self-perceived change. Otherwise, a 10 % change from baseline will be considered minimal change, while a 30 % change from baseline will be considered a substantial and clinically important change [37].

The Neck Disability Index (NDI) is a 10-item self-administered questionnaire, scored from 0 to 50 with a higher score representing more disability. A score of 0 to 4 represents no disability, a score >35 represents complete disability, and a score >25 represents severe disability. An absolute change of 10 points or relative change of 20 % on the NDI will be considered clinically important [38].

Feasibility to conduct a larger study will also be determined by estimating the effect size (and subsequently, the anticipated sample size) needed for a future main trial. Challenges encountered by participating clinicians while conducting the trial will be assessed by administering an end-of-study questionnaire and conducting interviews. An open-ended question will be used to elicit the chiropractors’ experiences (challenges or facilitators) encountered while trying to comply with the guideline recommendations.

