### Statistical analysis

The main analysis will focus on descriptive statistics relating to feasibility to estimate likely recruitment and retention rates, adherence to the intervention, and provide key parameters, e.g. effect size needed to decide on a primary outcome and to estimate the sample size for a full-scale study. Also, we will estimate the potential efficacy of the intervention on adherence to the recommended multimodal approach for NSNP and on patient outcomes of pain and disability. Instead of calculating an average response on each measure for each group and comparing means between groups, this study will identify the proportion of people in each group making a treatment response, which will then be compared between groups. Each person will be classified as having made a response, a deterioration, or no change on each measure based on a change equal to or greater than the MCID published or recommended for that measure. Table 4 provides the summary of this analysis.

**Table 4 Tab4:** Statistical analysis

Construct	Measure	Measurement scale
Feasibility of recruitment, retention, and data completion (both chiropractors and patients)	Recruitment and retention rates, missing data	Descriptive statistics: mean and SD for continuous variables and proportions for categorical variables
Chiropractor process outcomes		
Adherence rate	Single indicators	Continuous data (number of DCs adhering to the intervention per number of eligible participants)
	Composite	Count of indicators reaching “success” threshold
Behavioural	Level of knowledge and self-efficacy	5-point Likert scale (from 1 = strongly agree to 5 = strongly disagree), ordinal
Patient health outcomes		
Pain	Visual analogue scale	Self-rated level of pain on 11 points, continuous
Disability	Neck Disability Index	Scale range and subscales: 10 items in total; each item is scored from 0 to 5 (“0” = no disability and “5” = full disability) for a total of 50
Satisfaction with care	Questionnaire	Self-rated satisfaction with care measured on the short-form questionnaire rated on a 5-point Likert scale from “very satisfied” to very “dissatisfied”
Potential efficacy	Post-intervention between groups	Normal approximation to the binomial

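### As worded, the VAS MCID averages changes of opposite sign and conflicts with the responder rule, and the NDI cut-off does not say what its 20% refers to

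*Protocol article*

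**What the plan says.** All references are to the protocol article.

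- **Measures, VAS, anchor-based rule.** The MCID on the 10-cm VAS "will be measured as the mean difference between current and baseline scores among patient participants who report feeling either" slightly worse or slightly better on a global rating of change. No absolute value, sign reversal or separate estimate by direction is mentioned.
- **Measures, VAS, percentage rules.** The text continues: "Otherwise, a 10 % change from baseline will be considered minimal change, while a 30 % change from baseline will be considered a substantial" and clinically important one. What triggers the switch to these percentages is not stated.
- **Measures, NDI.** The index is "scored from 0 to 50 with a higher score representing more disability". The rule is: "An absolute change of 10 points or relative change of 20 % on the NDI will be considered clinically important". Whether 20% is of the patient's baseline or of the scale is not stated.
- **Statistical analysis, use of the cut-offs.** In place of comparing means, "this study will identify the proportion of people in each group making a treatment response, which will then be compared between groups". Each person is classed as a response, a deterioration or no change "based on a change equal to or greater than the MCID published or recommended for that measure".

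**The concern.** The change score is current minus baseline, so it is negative for a patient who improves and positive for one who worsens. A single mean over both kinds of patient does not measure the size of a minimal change; it measures the balance between the two groups. If that mean became the cut-off, it would be too small, and measurement noise would count as response or deterioration.

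The source of the cut-off is also inconsistent. Measures derives a VAS MCID from this trial's data, while Statistical analysis uses an external one. With the two percentages, the VAS has three candidate cut-offs, one of them known only after outcomes are seen. The NDI rule can mean two quite different things.

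The responder proportions are the stated between-group comparison for pain and disability, and the pilot is meant to supply effect sizes for the main trial. An unclear or undersized cut-off would carry into that planning.

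**Working it through.** **1. Signed pooling of VAS changes.** Let f be the share of anchor patients who feel slightly better, and m_b and m_w the mean sizes of change in the better and worse groups. The document gives none of these, so all values below are assumptions. Taken literally,

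pooled MCID = −f × m_b + (1 − f) × m_w.

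With equal sizes (m_b = m_w = m), its magnitude is m × (2f − 1) for f ≥ 0.5:

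| f | fraction of true size | m = 1.0 cm | m = 1.5 cm |
|---|---|---|---|
| 0.5 | 0% | 0.0 | 0.0 |
| 0.7 | 40% | 0.4 | 0.6 |
| 0.9 | 80% | 0.8 | 1.2 |
| 1.0 | 100% | 1.0 | 1.5 |

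With unequal sizes, balance can occur elsewhere. For m_b = 1.0, m_w = 1.5 and f = 0.6, the result is −0.6 + 0.6 = 0. Estimating each direction separately returns m_b and m_w whatever the mix.

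**2. Which VAS cut-off applies.** Set side by side, Measures offers a trial-derived value, 10% of baseline and 30% of baseline; Statistical analysis points to a published or recommended value and does not mention the derived one. At a baseline of 5 cm, 10% is 0.5 cm and 30% is 1.5 cm; the ratio is three at every baseline. As an illustration only, with no true change and an assumed SD of change of 2 cm, P(Z > 0.5/2) = 0.40 and P(Z > 1.5/2) = 0.23 would be classed as responders.

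**3. NDI.** The plan's own pair is checked first: 10/50 = 20%. The two criteria therefore agree exactly if 20% is of the scale range.

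If 20% is of baseline b, the relative cut is 0.20 × b. Measures says that "A score of 0 to 4 represents no disability", so the lowest whole-number baseline with any disability is 5; the eligibility criteria set no minimum NDI.

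| Baseline NDI | 20% of baseline (points) | 10 points ÷ relative cut |
|---|---|---|
| 5 | 1 | 10 |
| 10 | 2 | 5 |
| 15 | 3 | 3.3 |
| 20 | 4 | 2.5 |
| 25 | 5 | 2 |
| 35 | 7 | 1.4 |
| 50 | 10 | 1 |

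Since b ≤ 50, 0.20 × b ≤ 10 always. Any change of 10 points already meets the relative criterion, so under an either-or rule the 10-point criterion never reclassifies anyone. At baselines 5 to 9 a 10-point improvement is impossible, while a change of 1 to 1.8 points meets the relative rule.

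As an illustration, take baseline 15, no true change and a normal approximation. The proportion classed as responders at 3 points against 10 points is:

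- SD of change 6 (assumed): P(Z > 3/6) = 0.31 against P(Z > 10/6) = 0.05.
- SD 4: P(Z > 0.75) = 0.23 against P(Z > 2.5) = 0.01.
- SD 8: P(Z > 0.375) = 0.35 against P(Z > 1.25) = 0.11.

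**The case against.** The strongest reply is that the anchor-based MCID may never be meant as a cut-off. Statistical analysis says that published values classify patients, Measures cites a source beside the 10%/30% and NDI figures, and a pilot may reasonably estimate an MCID as a parameter for the main trial. The wording about the two groups could also be read as one mean per group, or as a mean size of change. On that reading no patient is misclassified. This largely stands as a limit on the harm: a reader might infer that a near-zero cut will classify every patient, but the document does not say that the derived value is the one used. It does not remove the point. Measures describes one MCID and one mean, introduces the percentages only as an alternative to it, and is not reconciled with Statistical analysis.

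On the NDI, 10 points is exactly 20% of the scale, so the authors may have meant one criterion stated twice. That is possible and cannot be excluded; the text does not say so.

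The same cut-off applies to both arms, so no between-group bias is shown. That is correct. The consequence is a responder proportion whose meaning depends on an unstated choice.

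Finally, pain and disability are secondary to feasibility and are also analysed by GEE. That stands and limits the severity.

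**Conclusion.** The point holds in a limited form and is of moderate severity. As written, the VAS MCID does not handle sign and is biased toward zero if followed literally. Its source conflicts with the classification rule, and the value that defines a VAS response is not fixed. The NDI rule either states one criterion twice or, if 20% is of baseline, contains a 10-point criterion with no effect.

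Three stronger conclusions that a reader might draw are not supported:

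- **That the VAS MCID will be zero.** This needs balanced contributions from the two groups, and the document gives neither the mix nor the sizes. With 70 to 90% feeling slightly better and equal sizes, both assumed, 40 to 80% of the true value remains.
- **That the cut-offs conflict by a fixed multiple such as five-fold.** Five-fold occurs only for the NDI at baseline 10 with 20% read as of baseline. The NDI ratio runs from 1 at baseline 50 to 10 at baseline 5, and there is no conflict if 20% is of the scale. The VAS 10% and 30% are labelled as different grades of change, so they do not contradict each other; the defect is that neither is named as the response cut.
- **That the feasibility conclusions are at risk.** No criterion in Table 1 uses these cut-offs, and the GEE models of repeated pain and disability measurements do not depend on them.

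What is affected is the pain and disability responder comparison and any effect size drawn from it for the main trial. The false-responder proportions above rest on assumed SDs and show direction, not a forecast.

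**What to change.** 1. In Measures, compute any anchor-based VAS MCID separately for patients slightly better and slightly worse, or reverse the sign of one group before pooling. Report it descriptively and do not use it to classify this trial's patients.
2. Reconcile Measures with Statistical analysis by naming one published cut-off per measure for the response, no change and deterioration classes. For the VAS, one option is the 30% that the protocol itself calls clinically important. The Trial status section reports that patient recruitment has begun, so the choice should be recorded before outcomes are analysed.
3. State one NDI criterion and say whether it refers to the scale or to the patient's baseline.

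The cost is a few sentences and no new data. Responder rates may be lower than under the looser readings. If a 10-point NDI rule is chosen, patients with baseline below 10 cannot be responders; this should be stated and their number reported.

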### Interventions

#### Development of the KT intervention

The science of KT research draws from a variety of behavioural and social science disciplines and employs new approaches and methods [39]. The proposed KT educational intervention was developed to facilitate the uptake of a recently developed guideline for the management of NSNP among chiropractors, the full details of which is published elsewhere [31]. To design the KT intervention, an expert panel used a systematic, theory-informed approach that was guided by the following key questions [40]:Who needs to do what, differently?Based on wording from the neck pain guideline itself, the target-specified behaviour is the chiropractors’ adherence to recommended care, i.e. Undertaking or recommending multimodal care for patients with acute and chronic NSNP.Using a theoretical framework, which barriers and enablers need to be addressed?Twenty-five chiropractors were invited to take part in telephone interviews guided by the Theoretical Domains Framework (TDF) [41] to specify modifiable barriers and facilitators to managing neck pain. The first 13 respondents from six Canadian provinces completed a 60-min interview. Transcripts were coded deductively by two independent assessors and reviewed by investigators. The results highlighted a number of potential barriers and facilitators to implementing a newly developed neck pain guideline targeting this professional group. Specifically, adherence to prescribing multimodal care was felt to be potentially influenced by nine key theoretical domains: (1) social influence; (2) environmental context and ressources; (3) reinforcement; (4) skills; (5) behavioural regulation; (6) knowledge; (7) memory, attention, and decision making processes; (8) social/professional role and identity; and (9) beliefs about consequences.Which intervention components could overcome the modifiable barriers and enhance the enablers?An expert panel mapped behaviour change techniques to barriers and enablers within key theoretical domains and identified relevant KT strategies and modes of delivery to increase the use of multimodal care among chiropractors [42].

#### Components of the intervention

Table 3 describes the components of the intervention package. Four key elements were designed to capture key theoretical domains, behaviour change techniques, and modes of delivery. The specific learning objectives of the intervention components are presented in Additional file 2.

**Table 3 Tab3:** Intervention components and modes of delivery

Key elements and topics	Delivery
(1) Three 50–60-min webinars containing didactic information on the following topics	
^a^Webinar 1. ^*^ Overview of what evidence-informed practice is and why CPGs are useful	CMCC continuing education (online)
Webinar 2. ^*^ Key recommendation of the new guideline on the management of non-specific neck pain	CMCC continuing education (online)
Webinar 3. ^*^ Introduction to self-management strategies and to the Brief Action Planning (BAP) model in particular	CMCC continuing education (online)
(2) Two online case scenarios each with care options to help apply recommendations as a proxy for daily practice with quizzes	Accessible on Fluid Survey after completion of the webinar 2 (neck pain guideline) at
	http://fluidsurveys.com/s/ClinicalVignette1 http://fluidsurveys.com/s/ClinicalVignette2
(3) A self-management video underpinned by the BAP model to demonstrate how clinicians can facilitate patient decisions about self-management strategies. The video portrays a clinician discussing active planning strategies with a chronic neck pain patient who chooses to increase his/her level of physical activity	Accessible online after completion of the webinar 3 (BAP) on the LMS of the CMCC through a link from the CCGI website at http://www.chiropractic.ca/guidelines-best-practice/Chiropractors/resources/physical-activity-ergonomics-public-health/

^a^Before watching webinar 1 on EIP, clinicians will be encouraged to complete three online modules (Evidence Informed Practice, Summary Research, and Assessing Summary Research) at http://www.csh.umn.edu/evidenceinformedpracticemodules/index.htm

*All three webinars were recorded between October 29 and November 26, 2014, for future diffusion to participants in the intervention group

#### Delivery of the intervention

Chiropractors consenting to participate will be allocated to receive either the KT strategies plus practice guidelines for the intervention group or practice guidelines alone for the control group. Modes of delivery of the webinars are outlined in Table 3. All webinars have been recorded and will be made available to participants allocated to the intervention arm.

#### Acceptability of the intervention to participants

Acceptability will not be assessed directly. However, adherence to multimodal care and initial rates of willingness to participate will be used as proxy measures of acceptability of the intervention to chiropractors and patients. It may be that the intervention and the trial processes will be acceptable to some participants (those who participated and adhered to the protocols) but not to others (those who chose not to take part, perhaps due to being put off by the intervention or the associated trial processes or by competing commitments). Post-randomization withdrawals in the control group may suggest that control participants are dissatisfied with their allocation. Reasons for not participating will be documented using a pre-defined checklist.

### Procedures

The CCA and provincial chiropractic associations will be asked to promote the study via their newsletters and by emails to chiropractors informing their members of the study purpose and encouraging them to participate in this study. An invitation letter with the McGill University letterhead, with a consent form, a demographic questionnaire, and a prepaid stamped and self-addressed envelope, will be sent to the sample of 200 chiropractors. Chiropractors expressing an interest in participating will receive a follow-up letter written in a standardized format, giving information about the study project. A follow-up invitation and a reminder to participate will be sent if initially an insufficient number of clinicians are enrolled. As an incentive to participate, chiropractors who complete all aspects of the study will be entered into a draw to win one of four $250 gift cards as a token of appreciation. In addition, most provincial chiropractic regulatory boards have pre-approved the KT intervention for 4 h of Continuing Education (CE). Certificates of completion are produced once the KT intervention is completed by chiropractors and all quizzes have been successfully answered. Obtaining a credit for the course may contribute to participant confidence regarding the experimental KT intervention and may improve study adherence.

In order to determine the eligibility of the participating chiropractors, a demographic questionnaire will be sent with the invitation package to inquire about their age, sex, years in practice, practice location (rural versus urban), chiropractic school attended, type of practice (solo versus multidisciplinary clinic), main chiropractic techniques/approaches used (e.g. diversified, Gonstead, BCP), and professional membership status.

#### Consent

A consent form will be completed by chiropractors (Additional file 3). Participating chiropractors will explain the study to patients and obtain informed consent from interested patients (Additional file 4). We do not expect that study participation will cause any harm to participants. If, at any time, participants decide they would like to withdraw, they will be able do so without any consequences to their routine management.

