## Methods/design

### Design

This is a pilot cluster-randomized, two-arm, parallel-group controlled trial with a 1:1 allocation ratio. A cluster-randomized design has been chosen to avoid contamination between intervention and control arms by individual patients who would potentially be served by the same chiropractor in a non-cluster design. In addition, cluster-randomized trials offer logistical convenience when implementing certain interventions such as training, feedback, and supervision programmes, which are easier to administer to groups rather than individuals [32].

The study will test the feasibility and impact on protocol adherence and patient outcomes of two methods of delivering an educational intervention: (1) a KT complex intervention (theory-based KT intervention that includes three webinars, two case scenarios followed by a quiz, and Brief Action Planning) plus dissemination of practice guidelines for the intervention group and (2) passive dissemination of a practice guideline alone for the control group.

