### Subjects/population

#### Recruitment of chiropractors

A sampling frame of 8200 chiropractic practices within 10 provinces in Canada will be obtained from the Canadian Chiropractic Association (CCA). From this, a random sample of 200 chiropractors will be selected and approached for participation in this study [33, 34]. A sample of 200 chiropractors has been chosen as we expect that 20 % of eligible chiropractors will agree to participate (i.e. recruitment rate), and from these, 80 % will complete the study at 3 months (retention rate). Chiropractors who agree to participate and meet the eligibility criteria will be randomized. If we are unable to recruit the required sample of 30 from the first wave of 200 chiropractors, an additional 200 chiropractors will be randomly sampled.

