#### Recruitment of patients

Participating chiropractors will each recruit up to five consecutive new patients with neck pain. A recruitment/advertisement notice will be posted in each participating chiropractor’s waiting room. The expected recruitment of 5 patients within 3 months is reasonable assuming an average practice volume of 85 patient visits per week per chiropractor, of whom 25 % are expected to have neck pain [6].

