#### Blinding

Investigators not involved in the delivery of the intervention and the study statistician will be blinded to group allocation until the statistical analysis has been completed. Participating chiropractors will be aware of the KT interventions they are receiving/implementing; otherwise, they will not be explicitly informed of their assigned groups. Participating chiropractors will be instructed not to tell their patients about their KT interventions so as to maintain patient blinding. Participating chiropractors will also be kept blind to all study hypotheses.

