#### Logistics of multicentre procedures

Challenges in recruiting patients across practices will highlight possible difficulties with implementing a multicentre trial. To increase the likelihood of successful recruitment, participating chiropractors will be encouraged to appoint a single staff member who will be responsible for local trial operationalization and recruitment.

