### Trial status

At the time of writing, 45 chiropractors have agreed to participate in the study and have been randomized to the intervention and control groups. Participants have started recruiting neck pain patients. Results are expected in May 2016.

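### Chiropractors who know which training package they received recruit and consent their own patients after randomization, so the pilot's patient effect estimates are open to recruitment bias of unknown direction and size

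*Protocol article*

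**What the plan says.** The Design section describes the trial: "This is a pilot cluster-randomized, two-arm, parallel-group controlled trial with a 1:1 allocation ratio". The chiropractor is the unit of randomization. Under Recruitment of chiropractors, "Chiropractors who agree to participate and meet the eligibility criteria will be randomized"; no step requires patients to be identified first. Trial status confirms the order: 45 chiropractors "have been randomized to the intervention and control groups. Participants have started recruiting neck pain patients".

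Enrolment of patients lies with the randomized chiropractor. "Participating chiropractors will each recruit up to five consecutive new patients with neck pain" (Recruitment of patients), and "Participating chiropractors will explain the study to patients and obtain informed consent from interested patients" (Consent). On what they know, the Blinding section says: "Participating chiropractors will be aware of the KT interventions they are receiving/implementing; otherwise, they will not be explicitly informed of their assigned groups". It adds that they are kept unaware of the hypotheses and asked not to tell patients about the training. Under Logistics of multicentre procedures, "participating chiropractors will be encouraged to appoint a single staff member who will be responsible for local trial operationalization and recruitment"; this is encouraged, not required.

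The patient results have a planned use. The Measures section derives an effect size and a sample size for the main trial. The Statistical analysis section compares between arms the proportions of patients whose change reaches the minimal important difference, and applies GEE to pain and disability.

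**The concern.** In a cluster trial, randomization balances the clusters. It balances the patients only if enrolment does not depend on the arm. Here the person who makes the diagnosis, applies the consecutive rule, explains the study and takes consent has already received either a printed guideline alone or that guideline plus webinars, vignettes and a self-management video. Training in exercise and self-care may change which patients are approached, how the study is presented, or who is interested. Eligibility covers acute and chronic pain of any duration, so there is room for case mix to drift apart.

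At stake are the patient-level effect estimates, any by-arm reading of patient recruitment, and the main-trial sample size built on them. A difference in who was enrolled could pass for a treatment effect, or could hide one.

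**Working it through.** **The plan's own figures.** 30 chiropractors × 5 patients = 150. 200 invited × 0.20 = 40 chiropractors, and 40 × 0.80 = 32, which covers the required 30. All reproduce; this point disputes none of them.

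**Where each safeguard acts.**
- Concealment of the allocation sequence separates the sequence generator from the coordinating staff. It protects the assignment of chiropractors, not the later enrolment of patients.
- The consecutive rule is applied by the chiropractor who knows the package, and the article states no check on it.
- The staff recruiter is optional and is not described as blinded.
- Blinding of patients and of hypotheses reduces deliberate selection. It does not stop the training itself from changing who is approached.
- Table 2 defines patient eligibility and participation rates, but the note under it promises comparison by arm only for retention and adherence.

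**Illustration for means (all inputs assumed).** Let there be no true effect, let intervention-arm patients be enrolled milder by d baseline SDs, and let the baseline to 3-month correlation be r.
- Bias in the 3-month difference = −r × d.
- Bias in the difference in change (3-month minus baseline) = −r × d + d = (1 − r) × d.
- With r = 0.5, d = 0.15, 0.25 and 0.40 give −0.075, −0.125 and −0.20 SD for the 3-month score, and +0.075, +0.125 and +0.20 SD for the change score. A simulation of 75 v 75 patients (1,500 runs) gave −0.075, −0.121, −0.199 and +0.074, +0.124, +0.201.
- The signs are opposite. The 3-month score would flatter the intervention; the change score would show less improvement and mask an effect.
- The baseline-adjusted bias is about 0, but by construction, because the imbalance was placed entirely in the measured baseline. If the enrolled patients instead differed by a stable amount d at both times, the adjusted difference would keep a bias of −d + r × d = −(1 − r) × d, or −0.125 SD at d = 0.25.
- Where adjustment applies, residual variance falls by the factor 1 − r² = 0.75.

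**Illustration for responders (all inputs assumed).** Bias = shift in acute share × (acute − chronic responder rate).
- Mildest case: 0.10 × (0.6 − 0.4) = 0.02. Most extreme: 0.30 × (0.7 − 0.3) = 0.12.
- If the true difference were 15 points from a base of 0.50, the main trial would need 170 per arm before inflation for clustering (two-sided 0.05, 80 % power). Planning on 17 or 27 points would give 131 or 49 per arm, with true power of 69 % or 32 %.
- A shift the other way would understate the effect.

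**Link to the responder definition.** The Measures section uses partly relative thresholds. A 20 % NDI change is 0.20 × 10 = 2 points from a baseline of 10, and 0.20 × 40 = 8 points from a baseline of 40. Baseline severity thus enters the classification directly.

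**The case against.** The strongest reply is that this is a pilot whose primary outcomes are feasibility rates, and that recruiting through practices is itself under test. Patients must be new and consecutive, a waiting-room notice is posted, office personnel assess language at screening, reasons for not participating go on a checklist, and Table 2 already needs the eligible and participating counts. All of this stands and keeps the point moderate.

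It is also fair that a condensed article may leave model covariates to the analysis plan, and that baseline scores are among the repeated measurements given to the GEE. The absence of a covariate list is therefore not the error here. But if baseline is modelled as an outcome and the effect is read from the arm-by-time term, that term estimates a difference in change and carries the (1 − r) × d bias shown above.

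Four stronger readings are tempting and not supported:
- That chiropractors are told their allocation. The Blinding section says they are not explicitly told their group; they know only which package they received.
- That the effect will be inflated. The direction is unknown, and the change-score illustration points the other way.
- That recruitment counts are not planned or will not be shown by arm. Table 2 defines them, and the participant flow figure is not visible.
- That 0.07 to 0.20 SD is the expected bias in this trial. The inputs are assumed, and the planned responder comparison is not what was simulated.

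**Conclusion.** The point holds in limited form. On the stated sequence, clinicians who know which package they received select and consent their own patients after randomization, and the stated safeguards reduce but do not close the route to differential enrolment. The patient pain and disability estimates are therefore open to recruitment bias whose direction and size cannot be determined from the documents. The ranges above (0.07 to 0.20 SD for means, 2 to 12 percentage points for responder differences) show only what assumed imbalances would do. The article's limitations do not mention the risk. The chiropractor-level feasibility rates, which are fixed before patient enrolment or do not depend on case mix, are largely untouched. Improvement is worthwhile because most of the data needed are already collected.

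**What to change.** (a) In Statistical analysis, estimate the 3-month between-arm effects on pain and NDI in the GEE with the patient's baseline VAS or NDI as a covariate. Use the same covariate in a cluster-adjusted model for the patient responder comparison.

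(b) Extend the by-arm comparison under Table 2 from retention and adherence to patient eligibility and participation rates, and report baseline VAS, NDI and acute or chronic status by arm.

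(c) In Study limitations, name the risk and state that adjustment removes only measured imbalance and not, for example, differences in motivation. Do not size the main trial on the pilot's patient effect alone.

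Requiring clinic staff to screen and consent patients before the consultation is not recommended here. Eligibility needs a clinical diagnosis and the exclusion of red flags, the article does not assure that staff are unaware of the arm, and recruitment has started.

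The cost is minor extra analysis and reporting. Table 2 already needs the counts, baseline VAS and NDI are already collected, and acute or chronic status is part of the eligibility criteria. All three parts can be done with recruitment under way.
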